# Berberine prevents postoperative recurrence of colorectal cancer: a protocol for a multicenter, double-blind, randomized controlled trial

**DOI:** 10.3389/fmed.2026.1908350

**Published:** 2026-08-13

**Keywords:** berberine, colorectal cancer, protocol, randomized controlled trials, recurrence

## Abstract

**Introduction:**

Postoperative recurrence and metastasis of colorectal cancer (CRC) are critical factors affecting long-term survival, and how to prevent postoperative recurrence and metastasis remains an urgent clinical challenge. Studies indicate that berberine has a preventive effect against colorectal adenoma recurrence; however, no research has yet investigated its preventive efficacy against CRC. This trial aims to evaluate the clinical efficacy and safety of BBR in preventing postoperative recurrence and metastasis of CRC by comparing it with a placebo group.

**Methods and analysis:**

This trial is a multicenter, randomized, controlled, double-blind clinical study. A total of 306 eligible patients with stage IIIB, IIIC CRC who had undergone surgery will be randomly assigned in a 1:1 ratio to the placebo group and the trial group. The primary outcome is 2-year disease-free survival (DFS) rate, while secondary outcomes include 1-year and 2-year postoperative recurrence rates of CRC, as well as the incidence of adverse reactions. We expect that this randomized controlled trial (RCT) will provide high-quality evidence on BBR for the prevention of postoperative recurrence of CRC, which can achieve more significant clinical benefits to patients with stage IIIB, IIIC CRC.

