### Sample size

2.4

This is a RCT with the BBR group as the intervention group and the placebo group as the control group. The 2-year DFS rate in postoperative CRC patients was set as the primary endpoint. According to our previous small-sample observations and literature review, the 2-year DFS rate was estimated to be 67% in the control group and 77% in the intervention group (4). A 1:1 parallel-group design was adopted, with a two-sided type I error α = 0.05 and a test power (1–β) = 0.8. Sample size calculation was performed using PASS 2021 software, yielding a required sample size of 316 patients in the intervention group and 316 patients in the control group. Considering a 15% dropout rate due to loss to follow-up and refusal, at least 363 patients were needed in each group, resulting in a total target sample size of 726 patients.

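### The abstract randomises 306 patients but section 2.4 requires 726; at 306, power for the planned effect is about 50%, not 80%

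*Protocol article*

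**What the plan says.** The abstract of the protocol article (Methods and analysis) states: "A total of 306 eligible patients with stage IIIB, IIIC CRC who had undergone surgery will be randomly assigned in a 1:1 ratio". That is 153 per arm.

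Section 2.4 (Sample size) derives a different number. It assumes that "the 2-year DFS rate was estimated to be 67% in the control group and 77% in the intervention group", "with a two-sided type I error α = 0.05" and "a test power (1–β) = 0.8". It reports the result as "yielding a required sample size of 316 patients in the intervention group and 316 patients in the control group", which is 632 in all. It then adds an allowance ("Considering a 15% dropout rate due to loss to follow-up and refusal") and concludes that "at least 363 patients were needed in each group, resulting in a total target sample size of 726 patients".

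These are the only two totals in the article. Nothing presents 306 as a pilot, a stage, an interim look or an evaluable subset.

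**The concern.** One trial cannot have two recruitment targets that differ by a factor of 726 / 306 = 2.4. The article gives only one power basis, in section 2.4, so a reader who takes 306 from the abstract will attach the 80% to it. If 306 is what will be enrolled, a true 10-point benefit would be missed about half the time. A null result would then say little about whether berberine works. If 726 is the target, the abstract, which is the part most people read, understates the trial by 420 patients.

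The question is live. Section 3.1 says recruitment has begun, and section 2.5.1 says numbered blinded drug was allocated to centres beforehand. Neither section states a number, so the article does not show which total the operations follow. The two totals imply very different recruitment. Section 3.1 runs from 1 February 2026 to 31 December 2028. For every patient to complete two years after randomisation, enrolment must end by about 31 December 2026, which is 11 months. That requires 726 / 11 = 66 patients a month, or 306 / 11 = about 28.

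**Working it through.** **Inputs** (section 2.4 unless noted): control p1 = 0.67; intervention p2 = 0.77; difference d = 0.10; two-sided α = 0.05 (z = 1.960); power 0.80 (z = 0.842); 1:1 allocation; 15% dropout. Section 2.7.1 defines the primary endpoint as a proportion at 2 years, so a two-proportion test matches it. The competing total, 306, is from the abstract.

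**1. Reproduce the plan's own figure.** For the pooled two-proportion z-test without continuity correction:

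n per arm = [1.960 × √(2·p̄·(1 − p̄)) + 0.842 × √(p1(1 − p1) + p2(1 − p2))]² / d²

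- p̄ = (0.67 + 0.77) / 2 = 0.72, and √(2 × 0.72 × 0.28) = √0.4032 = 0.6350
- √(0.67 × 0.33 + 0.77 × 0.23) = √0.3982 = 0.6310
- n = (1.2445 + 0.5311)² / 0.01 = 315.3, rounded up to **316 per arm**

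This matches section 2.4. The dropout step also reproduces: 316 × 1.15 = 363.4, stated as 363 per arm and 726 in total. (Dividing by 0.85 would give 372 per arm and 744 in total. That is a separate, smaller matter.)

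**2. Power at the abstract's total.** With the same formula solved for power:

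power = Φ[(d·√n − 1.2445) / 0.6310]

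| n per arm | Basis | d·√n | Power |
|---|---|---|---|
| 316 | section 2.4, before dropout | 1.7776 | 80.1% |
| 153 | 306 / 2, no loss | 1.2369 | 49.5% |
| 130 | 306 × 0.85 / 2 | 1.1402 | 43.4% |

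**3. Does another method rescue 306?**

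| Method | 153 per arm | 130 per arm |
|---|---|---|
| Pooled | 49.5% | 43.4% |
| Unpooled | 50.0% | 43.9% |
| Continuity-corrected | 44.4% | 38.0% |
| Schoenfeld, HR = ln 0.77 / ln 0.67 = 0.653 | 50.6% | 44.5% |
| One-sided 0.05 (not the plan) | 62.0% | 56.0% |

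No variant comes near 80%.

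**4. What 306 could detect with 80% power.** Holding control at 67%, 153 per arm needs 81.0% in the intervention arm (14 points), and 130 per arm needs about 82.1% (15 points). As a check, 67% versus 81% in the formula of step 1 gives (1.2158 + 0.5154)² / 0.14² = 152.9, that is 153 per arm.

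**The case against.** The strongest reply is that this is a stale figure in the abstract. Section 2.4 has a full derivation and an explicit total, while 306 appears once without one. The article attaches 80% power to 316 per arm, where it is correct, and never to 306. Moreover, 306 is exactly what 67% versus 81% would need before dropout, so it may come from an earlier effect assumption. If so, one number in the abstract changes and no power is lost.

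Much of this stands. The power loss is conditional on 306 being enrolled, and the article does not show that it is. The match with 67% versus 81% is suggestive, but it is an inference: the article states no such assumption, and the match cannot show which total is in force. None of this removes the contradiction, because both figures are current text and at least one is wrong.

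Two further limits are fair. The 43% assumes that the 15% dropouts leave the analysis. That fits the inflation in section 2.4, but section 2.9 allows last observation carried forward for dropouts. Also, the registration record, randomisation list and drug-supply records are not in the article, so whether they need correcting is unknown.

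**Conclusion.** The concern holds and must be fixed. It is an internal inconsistency in the trial's main design number, not an error in the 316-per-arm calculation, which is right on its own inputs. The abstract's 306 cannot be reached from the stated assumptions. If it is the operative target, power for 67% versus 77% at two-sided 0.05 is about 50% with complete data, and about 43% if 15% are lost from the analysis. These figures rest on the section 2.4 rates, the pooled two-proportion test that reproduces the plan's 316, and equal allocation. If 726 is operative, the stated power is not affected by this point and the error is confined to the abstract.

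**What to change.** Decide which total governs and state it identically in the abstract and section 2.4. Check the registration, randomisation list and drug supply against it, and correct any that differ.

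- **If section 2.4 governs:** change 306 in the abstract to the section 2.4 total.
- **If 306 governs:** rewrite section 2.4 to give 153 per arm. Replace the 80% power statement with about 50% for 67% versus 77% (about 43% after 15% loss), and report the difference detectable with 80% power (14 points, or 15 after loss). Do not change the assumed effect merely to recover 80% unless the new value has its own justification.

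The first route costs a text correction, plus a registry update if the registry carries the wrong figure. The second also costs the 80% claim, and the authors would have to say openly that a null result could not rule out a 10-point benefit. Neither route requires extra patients to correct the statement.

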**Ethics and dissemination:**

This study has been approved by the institutional review board of The Second Affiliated Hospital of Zhejiang Chinese Medical University (No. 2025-246-IH01).

**Clinical trial registration:**

www.chictr.org.cn, identifier: ChiCTR2600117441.

## Introduction

1

Colorectal cancer (CRC) represents one of the most prevalent malignant tumors of the digestive tract worldwide and remains a leading cause of cancer-related mortality (1). Recent data from the National Cancer Center (2022) indicate that in China, CRC ranked the second highest incidence among malignant tumors (approximately 10.72%), with a mortality rate ranking fourth (approximately 9.32%), posing a significant public health burden (2). While advances in medical technology have improved early diagnosis and surgical resection rates, postoperative recurrence continues to substantially limit patient survival Clinical evidence shows that approximately 40% of stage III CRC patients experience tumor recurrence and metastasis following radical surgery and standard adjuvant chemotherapy (3). Additionally, the 2-year disease-free survival (DFS) rates demonstrated considerable variation across disease stages: approximately 80% for stage III overall, 79% for stage IIIB, and only 60% for stage III C (4). These findings underscore the urgent need for effect strategies to prevent postoperative CRC recurrence.

Currently, prevention of postoperative recurrence of CRC primarily involves adjuvant antitumor therapy and lifestyle interventions. Evidence suggests that weight management, healthy lifestyle practices, and a diet rich in vegetables, fruits, and whole grains may improve survival outcomes (5). Meanwhile, multiple clinical trials have actively explored therapeutic interventions to reduce recurrence risk-including vitamin D supplementation, postoperative anticoagulation, and nonsteroidal anti-inflammatory drugs (NSAIDs) like aspirin, none have demonstrated their efficacy in large-scale RCTs (6–8). Notably, targeted regulation of gut microbiota has become a research hotspot in the prevention and treatment of CRC progression. Intestinal microbiota dysbiosis appears significantly associated with postoperative recurrence, potentially through mechanisms involving chronic intestinal inflammation secondary to microecological imbalance (9–11).

Traditional Chinese medicine (TCM) has gained increasing recognition in comprehensive cancer care, particularly for its potential to enhancing treatment efficacy while reducing toxicity. Furthermore, guided by the TCM principle of “preventive treatment of disease” and leveraging its multi-target, multi-pathway regulatory strategies, TCM combined with precision medicine may offer novel strategies for postoperative CRC management. Clinical data suggest that long-term TCM administration may reduce CRC recurrence and metastasis risks (12). Specifically, Coptidis Rhizoma, as a commonly used traditional Chinese medicine in clinical practice among CRC patients, especially in those with diarrhea (13). Berberine (BBR) is the main active ingredient of, Coptidis Rhizoma and has shown promising prospects in the treatment of CRC. Clinical trials have shown that BBR can reduce colorectal adenomas recurrence (0.3g twice daily for two consecutive years) with favorable safety profiles (14). Additionally, several studies have confirmed that BBR exerts a significant inhibitory effect on the progression of colorectal adenoma and CRC (15–17). In addition, BBR may be able to overcome cetuximab resistance in CRC, thereby achieving a synergistic effect (18).

Based on the above research findings, our research team has systematically investigated BBR's mechanism in CRC models. Using AOM/DSS-induced inflammation-associated carcinogenesis models, we demonstrated BBR's capacity to inhibit CRC progress by gut microbiota-mediated short-chain fatty acid modulation (19). Building on TCM theory regarding dietary impacts we utilized AOM/DSS to established a CRC model, simulating internal damp-heat syndrome with a high-fat diet. The results identified that BBR significantly upregulated beneficial bacteria, such as Akkermansia and Bifidobacterium and modified lipid metabolism pathways, thereby attenuating high-fat diet-induced CRC progression (16). Additionally, we mechanistically confirmed BBR's protective effects against chemotherapy-induced intestinal mucosal injury via the gut microbiota-mediated PI3K/AKT/mTOR pathway, showing synergistic antitumor effects with 5-Fu (20). However, robust evidence regarding BBR's efficacy in preventing postoperative CRC recurrence remains limited.

## Methods and analysis

2

### Objectives

2.1

The primary objective is to evaluate the clinical efficacy and safety of BBR in preventing postoperative recurrence of stage IIIB/IIIC CRC. The secondary objectives are to elucidate the key mechanisms underlying BBR in preventing postoperative recurrence of CRC from the perspectives of gut microbiota and metabolism, screen biomarkers for the early and precise prediction of postoperative recurrence, and provide key targets for the prevention and treatment of CRC progression in the future.

### Study design

2.2

This multicenter clinical trial will be conducted at four tertiary Grade A hospitals within the province. Patients who have undergone surgical resection for stage IIIB/IIIC CRC will be screened and enrolled. Eligible participants will be randomly assigned at a 1:1 ratio to two groups, receiving either oral BBR or placebo at a dosage of three capsules (0.1 g per capsule) twice daily for 12 consecutive months (Figure 1). All patients will receive adjuvant chemotherapy in accordance with standard guideline-based regimens during the study period. Clinical and laboratory data will be collected at baseline, during treatment, and the follow-up phase. This study follows the Declaration of Helsinki and has been approved by the medical ethical committee of the Second Affiliated Hospital of Zhejiang Chinese Medical University (No. 2025-246-IH01). It has been registered on Chinese Clinical Trial Registry: ChiCTR2600117441. This trial protocol was designed and reported in accordance with the SPIRIT 2025 statement. The corresponding checklist is available in the Supplementary material.

**Figure 1 F1:**
[figure not shown]
The flow chart of clinical research.

### Eligibility criteria

2.3

#### Diagnostic criteria

2.3.1

The diagnosis of CRC is based on the Chinese Guidelines for the Diagnosis and Treatment of Colorectal Cancer (2023 Edition) (21), and staging is performed according to the 8th edition of the AJCC TNM staging system.

#### Inclusion criteria

2.3.2

(1) Patients with pathologically confirmed stage IIIB or IIIC CRC after radical resection, receiving initial treatment;(2) Aged from 18 to 75 years;(3) ECOG performance status score less than 2 (22);(4) Patients who initiate adjuvant chemotherapy within 6 weeks after radical resection of CRC;(5) No local or distant tumor recurrence was determined by imaging;(6) Patients with good communication ability who can comply with the study protocol and complete the study procedures;(7) Patients who have voluntarily signed the informed consent form after fully understanding the study purpose and procedures, disease characteristics, drug effects, related examinations, and potential risks/benefits of this study.

#### Exclusion criteria

2.3.3

(1) Patients with severe cardiac, hepatic or renal diseases;(2) Patients with a personal history of other malignancies within 5 years;(3) Patients with mental disorders, disturbed consciousness or inability to communicate verbally;(4) Patients with drug allergy or intolerance;(5) Pregnant women, lactating women or women intending to become pregnant;(6) Psychiatric patients who are uncooperative.

#### Termination criteria

2.3.4

(1) Voluntary withdrawal or loss to follow-up by the patient;(2) Inability to continue participation due to serious adverse events;(3) Failure to comply with the study plan to complete the scheduled medication treatment and follow-up arrangements:
1) Investigational drug: For medication adherence assessment in chronic disease studies, the internationally accepted standard is between 80 and 120%. In this study, follow-up visits are conducted every 3 months. Using an illustrative example, the actual number of pills taken (A) is calculated by subtracting the number of pills returned at the visit from the number previously dispensed. The expected pill count is 90 × 2 × 3 = 540pills, yielding an acceptable adherence range of 80% × 540–120% × 540, i.e., rounded to 432–648 pills. If A falls outside this range, the patient is considered non-adherent and will be regarded as a dropout.2) Chemotherapy: According to the CSCO guidelines, postoperative adjuvant chemotherapy for stage IIIB, IIIC colorectal cancer should last 4–6 months. Therefore, patients who are intolerant to chemotherapy and receive it for ≤ 3 months will be regarded as dropouts, as this may increase the risk of recurrence and metastasis.

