#### Outcome measures

2.7.1

The primary endpoint is 2-year disease-free survival, defined as the proportion of enrolled patients who develop disease recurrence or death within 2 years following randomization. Recurrence is categorized as either local or distant. Local recurrence is defined as the histologically confirmed reappearance of tumor consistent with the primary lesion at the anastomosis, adjacent bowel, surgical incision, mesentery and lymph nodes, abdominopelvic peritoneum, or retroperitoneum. Distant recurrence refers to metastatic spread of the tumor to distant organs including the liver, lungs, brain, and other extrapelvic sites.

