**Figure 2 F2:**
[figure not shown]
NCI-CTCAE Diarrhea Grading Scale. This table is based on the National Cancer Institute's (https://dctd.cancer.gov/research/ctep-trials/for-sites/adverse-events) Common Terminology Criteria for Adverse Events (NCI-CTCAE v5.0) (36), the standard classification used in oncology . ADL, activities of daily living. Definition: A disorder characterized by an increase in frequency and/or loose or watery bowel movements. ^a^Instrumental ADL refers to preparing meals, shopping for groceries or clothes, using the telephone, managing money, etc. ^b^Self-care ADL refers to bathing, dressing and undressing, feeding self, using the toilet, taking medications, and not bedridden.

Meanwhile, due to factors such as chemotherapy, subjects may experience grade 2 or higher diarrhea during the study period, so we need to be highly cautious and develop effective treatment plans in advance. When grade 2 or higher diarrhea occurs, emergency medications such as smectite powder, loperamide, or octreotide, should be administered after evaluation by physician. The investigator must record in the CRF detailed information, including the diarrhea grade, name of the rescue medication, dosage, and time of administration. If the patient experiencing Grade 3 diarrhea, the investigational drug will be temporarily discontinued until the toxicity resolves to Grade 1 or baseline, upon which it may be resumed. In addition, once a patient experiencing Grade 4 diarrhea, the investigational drug must be permanently discontinued and the subject discontinue the study.

During the follow-up period, regular assessments of tumor status will be performed, along with routine laboratory examinations including complete blood count, biochemical tests, and routine stool tests, as well as imaging examinations consisting of chest-abdomen-pelvis CT or contrast-enhanced abdomen-pelvis CT/MRI. For each quarterly follow-up visit, a window period of ±7 days is permitted. If a patient is unable to attend the hospital visit, conduct a telephone follow-up and remind the patient to complete the routine check-up. At the end of the 1-year follow-up period, a standard colonoscopy will be performed again, and blood and fecal samples will be collected.

In addition, if disease recurrence or metastasis occurs in the patient during treatment and follow-up, sample collection shall be performed at the time of recurrence and metastasis.

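### Three post-randomisation rules turn stopping or missing treatment into leaving the study, so later recurrences and deaths in these patients go unobserved for the 2-year primary endpoint

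*Protocol article*

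**What the plan says.** Three rules in the protocol article act after randomisation.

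- **Pill count (Section 2.3.4, Termination criteria).** The expected count for a 3-month interval is 540 tablets and the accepted range is 432 to 648. "If A falls outside this range, the patient is considered non-adherent and will be regarded as a dropout". The rule sits under the item "Failure to comply with the study plan to complete the scheduled medication treatment and follow-up arrangements".
- **Short chemotherapy (Section 2.3.4).** Patients who are intolerant to chemotherapy and receive it for 3 months or less "will be regarded as dropouts, as this may increase the risk of recurrence and metastasis". Both conditions, intolerance and short duration, are part of the rule.
- **Grade 4 diarrhoea (Section 2.7.3, Follow-up program).** "the investigational drug must be permanently discontinued and the subject discontinue the study". The same section orders a temporary hold of study drug for grade 3 diarrhoea.

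Against these stand the endpoint in Section 2.7.1, "defined as the proportion of enrolled patients who develop disease recurrence or death within 2 years following randomization", and the schedule in Section 2.7.2, which has assessments every 3 months for 2 years or until recurrence or metastasis. Section 2.9 permits, but does not require, last observation carried forward for dropouts, followed by a sensitivity analysis. Section 2.4 inflates the sample size with these words: "Considering a 15% dropout rate due to loss to follow-up and refusal".

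**The concern.** The primary endpoint needs the 2-year status of every randomised patient. The rules above end participation on events that occur after randomisation and that may be linked to prognosis, to treatment arm, or to both.

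The link to prognosis is the protocol's own for the chemotherapy rule: it gives a higher risk of recurrence as the reason for the rule. For non-adherence and grade 4 diarrhoea, higher risk is a reasonable inference that the document does not state.

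A link to arm is plausible. The Introduction reports that berberine has "protective effects against chemotherapy-induced intestinal mucosal injury", so chemotherapy tolerance and gut toxicity could differ between arms. That work was done in models, so it gives a reason to expect a difference but no estimate of one.

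At stake is a between-arm bias in the primary comparison that cannot be repaired at analysis, because the outcomes would not have been collected. A second consequence is that the 15% allowance names only loss to follow-up and refusal, not patients removed by these rules.

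**Working it through.** **1. The plan's own sample size.** Inputs from Section 2.4: 2-year DFS 67% v 77%, two-sided alpha 0.05, power 0.80, 1:1 allocation. The two-proportion formula with pooled variance and no continuity correction gives 316 per arm, exactly as stated. The plan then adds 15%: 316 × 1.15 = 363.4, stated as 363. The point is therefore not about the sample-size arithmetic.

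**2. Rules against endpoint.** Section 2.7.1 counts enrolled patients over 2 years. Section 2.7.2 names recurrence or metastasis as the only event that ends assessments early. Section 2.3.4 ends participation for pill count or short chemotherapy, and Section 2.7.3 does so for grade 4 diarrhoea. No sentence says that recurrence and death are still collected afterwards. The passages cannot all be followed as written.

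**3. Size of a possible bias.** The removal rates and prognoses here are assumptions; the document gives none. Let p be the true 2-year DFS of an arm, f the share removed while disease-free, and q the true 2-year DFS of those removed. Take no true effect, so p = 0.67 in both arms, and q from 0.40 to 0.60.

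If removed patients are excluded, observed DFS = (p − f·q)/(1 − f).

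| Removed, berberine v placebo | q | Berberine | Placebo | False difference |
|---|---|---|---|---|
| 20% v 10% | 0.40 | 73.75% | 70.0% | 3.75 points |
| 20% v 10% | 0.50 | 71.25% | 68.9% | 2.4 points |
| 20% v 10% | 0.60 | 68.75% | 67.8% | 1.0 point |
| 15% v 15% | 0.40 to 0.60 | 71.8% to 68.2% | the same | 0 |

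With 363 randomised per arm, the 20% v 10% case moves the two-sided rejection rate from 5% to between 5.8% (q = 0.60) and 17.9% (q = 0.40). Reversing the imbalance reverses the sign.

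If removed patients are instead carried forward as disease-free, observed DFS = p + f·(1 − q). For 20% v 10% the false difference is (0.20 − 0.10) × (1 − q), which is 6 points at q = 0.40 and 4 points at q = 0.60. Equal removal again gives none. Carrying forward keeps the denominator but does not remove the bias; in this example it is larger.

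**4. Power, only if dropouts are excluded.** From 363 per arm:

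- No loss: power 85.2%.
- 15% loss: 363 × 0.85 ≈ 309 per arm, power 79.2%. The required 316 is reached at a loss of 47/363 = 12.9%.
- 30% loss (assumed): 363 × 0.70 ≈ 254 per arm, power 71.0%.

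To show how quickly one rule could use up the allowance: if 5% of those remaining failed the pill count in each of four quarters (assumed), 1 − 0.95⁴ = 18.5% would be removed; at 10%, 1 − 0.90⁴ = 34.4%.

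**5. Grade 3 hold against pill count.** Three tablets twice daily is 6 per day. A hold of 18 days removes 18 × 6 = 108, and 540 − 108 = 432, exactly the lower limit. At 19 days the count is 540 − 114 = 426. A patient who followed the hold instruction for more than 18 days of a 90-day quarter, and took every other dose, would be classed as non-adherent and a dropout.

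**The case against.** The strongest reply is that the article never says dropouts are excluded from the analysis. The endpoint is written on enrolled patients, analysis sets are commonly left to an analysis plan that is not shown, and carrying forward is optional and followed by a sensitivity analysis. All of that stands. A reader might infer that higher-risk patients are struck from the primary comparison, or that Section 2.9 necessarily counts them as disease-free; the document supports neither. It also does not support calling all three groups higher-risk, since it says so only of the chemotherapy group.

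This does not dispose of the point. An analysis set defined elsewhere can put a patient back in the denominator, but it cannot supply a recurrence or death that was never recorded. Nor can a sensitivity analysis, beyond showing how much depends on assumptions.

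Four further limits are fair. Between-arm bias needs differential removal, and with equal removal the illustration shows none under no true effect. The power loss applies only under exclusion, because carrying forward leaves 363 per arm. The grade 3 collision needs a long hold, and the document does not say whether held doses count as expected. Finally, only the grade 4 rule says in terms that the subject leaves the study. For the other two this follows from their place under the termination criteria and the word dropout.

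**Conclusion.** The point holds in this form: Sections 2.3.4 and 2.7.3 end participation for three post-randomisation events, nothing continues outcome follow-up, and this conflicts with the endpoint and visit schedule in Sections 2.7.1 and 2.7.2. Later recurrences and deaths in these patients are lost under either way of handling them.

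The size and sign of any bias cannot be derived from the document. On the assumptions shown (no true effect, 67% DFS, 20% v 10% removed, DFS 40 to 60% among those removed), it is 1.0 to 3.75 points under exclusion and 4 to 6 points under carrying forward, against a planned difference of 10 points. If dropouts are excluded and total losses exceed the 15% allowance, power is below 80%, for example 71% at an assumed 30% loss. It would go too far to say that the randomised comparison is certainly lost or that power will certainly fall short. The matter must still be settled in the protocol, since uncollected outcomes cannot be recovered at analysis.

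**What to change.** Reconcile Sections 2.3.4 and 2.7.3 with Sections 2.7.1 and 2.7.2:

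1. Separate stopping study drug from leaving the study. State that a pill count out of range, early end of chemotherapy, or discontinuation of drug for toxicity does not end outcome follow-up.
2. Continue the scheduled 3-monthly outcome assessments to 24 months for all randomised patients unless they withdraw consent.
3. Include everyone as randomised in the primary analysis.
4. Use the pill-count and chemotherapy thresholds only to define a supportive per-protocol set.
5. Reconcile the grade 3 hold with the pill-count rule by removing doses held under the protocol from the expected count.

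No change to the clinical rules for stopping or holding study drug is proposed.

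The cost is an amendment to protocol and consent while recruitment is underway; the visits themselves are already planned. There is also dilution from off-drug patients, which should be stated openly. If 15% of the berberine arm stop and have control-arm DFS (assumed), berberine DFS is 0.85 × 77% + 0.15 × 67% = 75.5%. Power at 363 per arm is then about 72%, and 444 per arm would be needed for 80%. The sample-size section should say whether this is accepted or allowed for.

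### Read literally, one 3-month pill count outside 432–648 makes a randomised patient a dropout, with no check on adherence over the 12-month course

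*Protocol article*

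**What the plan says.** Section 2.3.4 (Termination criteria) of the protocol article states the standard: "For medication adherence assessment in chronic disease studies, the internationally accepted standard is between 80 and 120" per cent. It attaches no period to that standard. The next sentence gives the visit spacing: "In this study, follow-up visits are conducted every 3 months". The count A is obtained by "subtracting the number of pills returned at the visit from the number previously dispensed", and the calculation is introduced as an example. The expectation follows: "The expected pill count is 90 × 2 × 3 = 540pills", "yielding an acceptable adherence range of 80% × 540–120% × 540, i.e., rounded to 432–648 pills". The consequence is: "If A falls outside this range, the patient is considered non-adherent and will be regarded as a dropout".

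Section 2.2 (Study design) sets the course: "three capsules (0.1 g per capsule) twice daily for 12 consecutive months". The article gives no 12-month pill total, does not require a second failure, and does not say how pills returned late are counted.

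Three other places bear on the rule:
- Section 2.7.3 allows ±7 days around each quarterly visit and provides for study drug to be held during Grade 3 diarrhoea and possibly resumed.
- Section 2.4 attributes the 15% dropout allowance to loss to follow-up and refusal. Non-adherence is not named.
- Section 2.9 permits last observation carried forward for data missing because of dropout.

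**The concern.** The only range the article supplies is a quarterly one, and the stated consequence is pass/fail. Over 12 months that gives four occasions on which a patient may fall outside it, with nothing to set a single low count against the other three. A patient whose intake over the whole course is well inside 80–120% can therefore be classed as a non-adherent dropout.

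The rule sits under the termination criteria, so it bears on trial status as well as on description. A dropout whose later data are missing may have the 2-year DFS outcome filled in by last observation carried forward. Any adherent or per-protocol set built on the rule would also depend partly on single-quarter variation and on when leftover pills are handed back, rather than on exposure to berberine.

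**Working it through.** **Inputs.** From section 2.3.4: 90 days × 2 doses × 3 pills, range 80–120%. From section 2.2: 12 months of treatment, so four 3-month intervals at 6 pills per day. From section 2.7.3: visit window ±7 days. The number of pills dispensed per visit is not given; 540 is assumed where needed.

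**1. The plan's own figures.** 90 × 2 × 3 = 540; 0.80 × 540 = 432; 1.20 × 540 = 648. All reproduce.

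**2. The same percentages over the course.** Expected pills: 4 × 540 = 2160. Range: 0.80 × 2160 = 1728 to 1.20 × 2160 = 2592.

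**3. One low quarter.**
- Counts of 540, 540, 540, 425: the last is below 432. Total 2045; 2045/2160 = 94.7%.
- In general, three full quarters give 1620. A fourth count of 431 gives 2051/2160 = 95.0%; a fourth count of 108 gives 1728/2160 = 80.0%. Every count from 108 to 431 fails the quarter and meets 80% over the course.
- In days: (540 − 432)/6 = 18. More than 18 days without drug in one quarter, with full intake otherwise, takes A below 432. A study-drug hold under section 2.7.3 lasting longer than that would do so too, and the article does not say how such a hold is counted.

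**4. Leftover pills carried to the next count.** Assume 540 dispensed per visit, a steady 88% intake (475 taken, 65 left), all leftovers forgotten at month 3, and both lots returned at month 6 and charged to that count.
- Month 3: A = 540 − 0 = 540, inside the range.
- Month 6: A = 540 − 130 = 410 (75.9%), below 432.
- The two counts together: 950/1080 = 88.0%, the true value. Totals remove the artefact.
- For steady adherence a, the second count is 540(2a − 1), which is below 432 when a < 0.90. The artefact therefore changes the status of patients between 80% and 90%; those below 80% fail either way.

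**5. Visit timing alone.** With full intake, an interval with both visits shifted runs from 76 to 104 days: 76 × 6 = 456 and 104 × 6 = 624. Both lie inside 432–648, so a visit within the window does not cause a failure.

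**6. How many patients.** The documents give no adherence distribution, so this is assumption only. Quarterly adherence was simulated as normal, capped at 100%, for 400,000 patients.

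| Assumption | Fail at least one quarter | Below 80% over course | Fail a quarter but at least 80% over course |
|---|---|---|---|
| Mean 92%, SD 8 points, within-patient correlation 0.5 | 18.5% | 2.9% | 15.6% |
| Mean 90–95%, SD 6–10 points, correlation 0–0.8 | – | – | 1.3% to 47.6% |

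A second set of assumptions (mean 85–95%, between-patient SD 5 points, within-patient interval SD 5–15 points) gives 5% to 73%. Its denominator is different: only patients with at least 80% over the course. The spread shows that the figure is driven by the assumptions.

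**The case against.** The strongest case on the other side is that quarterly assessment is a legitimate design choice, and several stronger readings that a reader might infer are not supported.

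- **That the rule contradicts the 80–120% standard.** It does not. The article gives the standard no period, and the only interval it mentions nearby is the 3-month visit. The 12-month benchmark is a proposal of this review.
- **That the article expressly fails a patient at any one of four visits.** The text is less definite: "Using an illustrative example, the actual number of pills taken (A) is calculated by subtracting the number of pills returned at the visit". It never says that the count applies at every visit or that one failure is enough. That is the literal reading, because the only range in the text is the quarterly one, but it is not spelled out.
- **That late-returned pills by themselves make dropouts of everyone below 90%.** Unreturned pills can only raise A, to at most 540 if 540 were dispensed, so that visit passes. A failure needs every leftover missed at one visit, brought to the next, and charged there. A condensed article may leave that reconciliation to the full protocol.
- **That about 15.6% of patients would be wrongly labelled.** No input to that figure is in the documents.

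Two further objections stand. Loss of endpoint information comes from treating non-adherence as dropout at all, so changing the window alone would not cure it; the fix has to separate the two. And a cumulative ratio has its own weakness: 108 of 540 pills in one quarter still gives 80.0% over the course, a gap that a quarterly check would show.

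What survives is that the assessment period is not properly fixed, and that the text as it stands turns one low count into dropout status.

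**Conclusion.** The point holds as a badly fixed rule that is cheap to improve. On the literal reading of section 2.3.4, a single quarterly count outside 432–648 makes a randomised patient a dropout even when intake over the course is as high as 95.0%. That arithmetic assumes only four 90-day intervals and full intake in the other three. The carry-over example is conditional on 540 pills being dispensed per visit and on returns being charged to the later count. The number of patients affected is unknown; about 1% to 48% is the range under the assumed distributions, and no single value in it should be quoted as an estimate. The documents do not support calling the rule a contradiction of the adherence standard.

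**What to change.** In section 2.3.4:

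1. State that a single quarterly count outside 432–648 does not by itself make a patient a dropout.
2. Classify adherence once, for the analysis: (total pills dispensed − total pills returned over the treatment period) ÷ pills expected for that period, with 80–120% applied to the ratio.
3. Use the classification only to define an adherent or per-protocol set or a sensitivity analysis, and say that DFS follow-up continues for all randomised patients.
4. Keep the quarterly counts as recorded data and report them beside the cumulative ratio.
5. Reconcile the count with the study-drug holds in section 2.7.3, so that it is clear how pills not taken during a hold enter the calculation.

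**Cost.** A few rewritten sentences and the matching derivation, using the pill counts already collected; no new visits. There are two downsides. Final adherence status is known only at the end of treatment, and a cumulative ratio can mask one long gap, which is why item 4 is needed.
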